## Abstract

**Introduction:**

Infectious and immune-mediated encephalitides are important but under-recognised causes of morbidity and mortality in childhood, with a 7% death rate and up to 50% morbidity after prolonged follow-up. There is a theoretical basis for ameliorating the immune response with intravenous immunoglobulin (IVIG), which is supported by empirical evidence of a beneficial response following its use in the treatment of viral and autoimmune encephalitis. In immune-mediated encephalitis, IVIG is often used after a delay (by weeks in some cases), while diagnosis is confirmed. Wider use of IVIG in infectious encephalitis and earlier use in immune-mediated encephalitis could improve outcomes for these conditions. We describe the protocol for the first ever randomised control trial of IVIG treatment for children with all-cause encephalitis.

**Methods and analysis:**

308 children (6 months to 16 years) with a diagnosis of acute/subacute encephalitis will be recruited in ∼30 UK hospitals and randomised to receive 2 doses (1 g/kg/dose) of either IVIG or matching placebo, in addition to standard treatment. Recruitment will be over a 42-month period and follow-up of each participant will be for 12 months post randomisation. The primary outcome is ‘good recovery’ (score of 2 or lower on the Glasgow Outcome Score Extended—paediatric version), at 12 months after randomisation. Additional secondary neurological measures will be collected at 4–6 weeks after discharge from acute care and at 6 and 12 months after randomisation. Safety, radiological, other autoimmune and tertiary outcomes will also be assessed.

**Ethics and dissemination:**

This trial has been approved by the UK National Research Ethics committee (South Central—Oxford A; REC 14/SC/1416). Current protocol: V4.0 (10/03/2016). The findings will be presented at national and international meetings and conferences and published in peer-reviewed journals.

**Trial registration numbers:**

NCT02308982, EudraCT201400299735 and ISRCTN15791925; Pre-results.

Strengths and limitations of this studyThis will be the first randomised controlled trial to evaluate the effect of early intravenous immunoglobulin (IVIG) treatment in encephalitis from any cause in children, aiming to recruit a large sample size (N=308) across 30 hospitals.Outcome measures will use robust validated and internationally accepted assessment tools and all trial data will be assessed by blinded investigators.The trial is expected to provide data on the role of IVIG in reducing poor outcomes following encephalitis from any cause, which would impact on care pathways and individual patient decisions within the health services community, in the UK and internationally and will also inform on health and social care costs.Expected recruitment has been based on the reported UK incidence of encephalitis and a high and consistent recruitment rate is required across all centres due to the low disease incidence. While the trial is expected to recruit well at all sites, it is possible that there could be unexpected under-recruitment at one or more sites which would be a barrier to timely completion.Given that patients with all forms of encephalitis will be enrolled to the trial, a statistically significant effect may be masked if there is a benefit from IVIG in only one or some aetiological subgroups.

## Introduction

### Background and rationale

Encephalitis is inflammation of the brain parenchyma and manifests as a clinical syndrome characterised by a combination of encephalopathy, behavioural changes, fever, seizure and focal neurological deficits.^1^ In England, the population incidence for all-cause encephalitis is estimated at 5.23–8.66/100 000/year,^2^ with infants and adults >65 years being the most affected.^2^ Diagnosis is typically made by a combination of clinical, laboratory, neuroimaging and electrophysiological findings using an internationally agreed consensus definition.^1^
^3^ Infections, usually viral, are the most common cause of acute encephalitis, where the cause is identified. Immune-mediated forms of encephalitis, usually characterised by the detection of neuronal antibodies in serum and/or cerebrospinal fluid (CSF), have been described, although the proportion is not yet clear.^4^
^5^

Encephalitis causes significant morbidity and mortality with up to 7–20% death rate for certain types^6–8^ and up to 50% of survivors reporting deficits such as memory loss, seizures, learning disability and functional impairment after prolonged follow-up.^9–13^ The significant burden of the disease despite the current standard treatment highlights the need to identify strategies to reduce poor outcomes in patients with encephalitis. Encephalitis also imposes a substantial economic and resource burden on healthcare services. A review of encephalitis admissions to paediatric intensive care units showed an average length of stay of 4.3 days, with 75% of children requiring ventilation, and some requiring cardiovascular support (17%) and renal dialysis (6.5%).(Unpublished observations. [name]. A population based observational study of childhood encephalitis in children admitted to paediatric intensive care units in England and Wales). A UK study of encephalitis hospitalisations reported a mean length of stay of 34 days and a cost to the National Health Service of >£40 million/year.^2^

Notwithstanding the aetiology, the common pathophysiological process in infectious and autoimmune encephalitis is brain inflammation. There is evidence that intravenous immunoglobulin (IVIG) has a beneficial role in encephalitis from its therapeutic and prophylactic use in enteroviral encephalitis in the immunocompromised and in outbreaks of enterovirus-71 infections in Asia,^14^ as well as other infectious causes of encephalitis.^15–17^ Acute immune treatment, including IVIG, also appears to benefit adults and children with autoimmune encephalitis.^18^ Randomised controlled trials (RCTs) have demonstrated IVIG efficacy in a number of neurological conditions that share similar underlying inflammatory mechanisms to encephalitis even if different aetiologies.^19^ IVIG appears to inhibit complement binding, neutralise pathogenic cytokines, downregulate antibody production and modulate phagocytosis and T-cell function.^20^

In clinical practice, the use of IVIG in encephalitis varies. In the immune-mediated forms of encephalitis, IVIG is often used after a period of delay (by weeks in some cases), while the diagnosis is being confirmed. In other cases, IVIG is used as a last treatment option, usually after several days from hospital admission, where clinical improvement is slow. This delay may limit its benefit due to the brain inflammation, which has already occurred. The variation in practice is due to a lack of class 1 evidence to support the use of IVIG in encephalitis and it is currently unknown whether the wider use of IVIG in infectious encephalitis and earlier use in immune-mediated encephalitis could alter the outcome of this group of conditions. There is therefore the need to fill this evidence gap.

At present, there are no robust controlled trials in children to inform on the optimal treatment of encephalitis. Given the available evidence of possible beneficial role of IVIG, it is therefore important to undertake a trial to investigate the effect of IVIG for all children presenting with encephalitis, and optimise the use of this expensive and limited resource.

### Trial objectives and design

The *I*mmuno*g*lobuli*N i*n the *T*reatment of *E*ncephalitis (IgNiTE) trial is a multicentre, double-blind, placebo-controlled, parallel arm, RCT that will evaluate whether early treatment with IVIG provides benefit for children with a diagnosis of encephalitis, when compared with standard therapy alone. In the context of the IgNiTE trial, ‘early treatment’ is defined as administration of IVIG within 120 hours from presentation to any hospital or, for transferred patients, within 72 hours from admission to a recruiting hospital even if >120 hours since initial hospital presentation.

It is expected that the IgNiTE trial will generate first class evidence to inform clinical decisions regarding the use of IVIG for children with acute and subacute forms of infectious and inflammatory encephalitis.

### Primary objective

The primary objective is to compare neurological outcomes of children with encephalitis who have been treated with either IVIG or placebo, in addition to standard therapy.

### Secondary objectives

The secondary objectives are
to compare (1) clinical and (2) further neurological outcomes of children with encephalitis who have been treated with IVIG or placebo, in addition to standard therapy,to confirm the safety of IVIG treatment for children with encephalitis,to identify the proportion of children with immune-mediated encephalitis,to determine the effect of IVIG treatment on neuronal antibody levels in children with immune-mediated encephalitis.

### Tertiary objectives

The tertiary objectives are
to explore clinically relevant neuroimaging predictors of childhood encephalitis,to explore predictors of neurological outcomes in children with encephalitis,to explore radiological patterns associated with different types of encephalitis,to understand the host inflammatory pathways in encephalitis and the relationship with clinical parameters and the effect of IVIG treatment on these pathways.

## Methods

### Trial setting

The trial is planned to be conducted in ∼30 UK hospitals (tertiary and district general) (see online supplementary table S1).

10.1136/bmjopen-2016-012356.supp1supplementary tables

### Eligibility criteria

*Inclusion criteria (based on the International Encephalitis Consortium consensus case definition)*^1^
Age 6 weeks to 16 years old,Acute (within 24 hours) or subacute (24 hours to 4 weeks) onset of altered mental state (reduced or altered conscious level, irritability, altered personality or behaviour, lethargy) not attributable to a metabolic cause,At least two of:
fever >38°C within 72 hours before or after presentation to hospital,new or acute onset brain imaging consistent with encephalitis or immune-mediated encephalopathy,CSF white cell count (WCC) >4/microlitre,generalised or partial seizures not fully attributable to a pre-existing seizure disorder,new-onset focal neurological signs (including movement disorders) for >6 hours,EEG abnormality that is consistent with encephalitis and not clearly attributable to another causeandParent/guardian/legal representative consent to the patient participating in the trial.

Exclusion criteria

The patient will not be enrolled to the trial if any of the following apply, in addition to failure to meet all the inclusion criteria:
high clinical suspicion of bacterial meningitis or TB meningitis (eg, presence of frankly purulent CSF; CSF WCC >1000/microlitre; bacteria on Gram stain and/or culture),prior receipt of any IVIG product during the index admission,traumatic brain injury,known metabolic encephalopathy,toxic encephalopathy,hypertensive encephalopathy/posterior reversible encephalopathy syndrome,pre-existing demyelinating disorder; pre-existing antibody-mediated central nervous system (CNS) disorder; pre-existing CSF diversion,ischaemic or haemorrhagic stroke,children with a contraindication to IVIG or albumin,known hypercoagulable state,significant renal impairment defined as GFR of 29 ml/min/1.73 m^2^ and below (Chronic Kidney Disease Stage 4),known hyperprolinaemia,known to be pregnant,any other significant disease or disorder which, in the opinion of the investigator, may either put the participants at risk because of participation in the trial or may influence the result of the trial, or the participant's ability to participate in the trial,participants who are being actively followed up in another research trial involving an investigational medicinal product which has a potential immunomodulatory or neuroprotective effect,administration of trial treatment not feasible within the study timeline (120 hours from presentation to any hospital or, for transferred patients, 72 hours from admission to a recruiting hospital even if this is >120 hours from presentation to initial hospital) as determined by the trial team,any other condition which, in the opinion of the investigator, may interfere with the ability to fulfil trial requirements, especially relating to the primary objective of the trial (this includes plans to be outside the UK for more than 12 months after enrolment).

In addition, any patient who, in the judgement of the clinician and prior to enrolment, is thought will benefit from IVIG will not be enrolled.

### Interventions

Participants will be randomised to receive two doses of either human immunoglobulin (intervention group) or placebo (control group), in addition to standard therapy (see Methods: assignment of intervention). There will be no set trial definition of standard therapy and this may vary between hospitals since there are currently no established national clinical care pathways for these. Participants will receive 1 g/kg/dose, in weight-based dosing bands (see online supplementary table S2). The IVIG product is Privigen (CSL Behring), supplied in unlabelled as 10 g/100 mL vials. Privigen is a licensed product, further details are outlined in the Product Information^21^ and the Summary of Product Characteristics (https://www.medicines.org.uk/emc/medicine/21359). The placebo is 0.1% Human Albumin Solution (HAS) in 0.9% Sodium Chloride solution which will be manufactured in the Aseptic Production Unit (APU), Pharmacy department, Royal Liverpool and Broadgreen Hospital, Liverpool, UK under cGMP conditions, under its MIA (IMP) licence and also supplied as 100 mL vials. The placebo has been constituted using HAS so as to prevent unblinding.

Packaging and labelling of both trial treatments will also take place at the same location. Labelling, which is identical for both trial treatments, has been approved by the Medicines and Healthcare products Regulatory Authority (MHRA) and conform to Annexe 13 of Good Manufacturing Practice standards and Article 13.3 of Directive 2001/20/EC (http://ec.europa.eu/health/files/eudralex/vol-4/2009_06_annex13.pdf). The APU will provide Qualified Persons services and distribute both trial treatments to the Clinical Trials Pharmacy at each recruiting site where they will be stored under controlled conditions and from where they will be dispensed.

The trial treatment will be prescribed on the participant's drug chart by a clinician who has been delegated for this task and using the suggested wording ‘Immunoglobulin/Placebo for the IgNiTE trial’. In addition, a clinical trials prescription form will be completed. For effective management of the trial treatment stock, and to minimise wastage, individual doses may vary slightly. A dosing guide for participants ≥13.5 kg is provided in a Clinical Study plan and is shown in online supplementary table S2. Participants <13.5 kg will receive 1 g/kg, rounded to the nearest whole gram.

Both trial treatments will be administered intravenously by a nurse who has received relevant trial-specific and Good Clinical Practice (GCP) training, is trained to give intravenous infusions and trained in the recognition and treatment of anaphylaxis. The first dose will be given as soon as possible after enrolment, within the defined timelines (see the Trial objectives and design section). The second dose will be given 24–36 hours after the first dose. The administration rate for the trial treatment will be in line with the guidance outlined in the Summary of Product Characteristics (SmPc) for Privigen and local hospital practices for Privigen administration.

Blood and CSF samples will be obtained before and after administration of the trial treatment (see the Data collection methods section).

### Coenrolment

Participants in the IgNiTE trial may be coenrolled to another study where:
the study does not involve an investigational medicinal product (IMP),the study involves an IMP, which is not thought to have a potential immunomodulatory, or neuroprotective effect, as judged by the investigator.

Patients on the following treatment(s) may not be enrolled to the IgNiTE trial:
Long-term maintenance immunotherapy (defined as 14 days or more) or within 3 months of stopping. This includes (but not limited to) the following: steroids (>1 mg/kg/day), azathioprine, mycophenolate mofetil, methotrexate, monoclonal anti-inflammatory treatment, for example, rituximab, infliximab (or within 1 year of discontinuing such treatment).

### Outcomes

There are currently no established European core outcomes for encephalitis or acquired brain injury in existence (COMET Initiative website: http://www.cometinitiative.org, searched 22 February 2016). The selected outcome measures reflect recommendations by The American Academy of Neurology Common Data Elements Project for neurological assessment post traumatic brain injury in children (accessible @ http://www.commondataelements.ninds.nih.gov). The secondary outcome measures will support the data obtained from the primary outcome.

#### Primary outcome

The primary efficacy outcome is ‘good recovery’, defined as a score of 2 or lower on the Paediatric version of the Glasgow Outcome Score-Extended (GOSE-Peds), at 12 months after randomisation. The GOS-E Peds is a modified version of the GOSE, a gold standard for measuring traumatic brain injury outcome in adults. The GOS-E Peds provides a developmentally appropriate structured interview necessary to evaluate children across different age groups, and it provides a valid measure of outcome in infants, toddlers, children and adolescents. Its use has been validated and found to be sensitive to severity of injury and to recovery over time, at least 6 months after brain injury and has been suggested as useful in guiding treatment in the early phases of recovery from brain injury.^22^ A strong correlation is also seen with parent report of functional outcomes and also with most performance-based cognitive tests for younger and older children. A 6-month assessment has also been chosen (see secondary objectives) as this has the advantage of improved trial retention, and earlier impact assessment.

#### Secondary and tertiary outcomes

These are outlined in table 1.

**Table 1 BMJOPEN2016012356TB1:** Secondary and tertiary outcomes

Data collection time point	Outcome measure
*Secondary outcomes*	
Clinical and neurological	
During hospital inpatient stay	Glasgow coma score Neurological examination findings as documented by the clinical team Duration of invasive ventilation (if ventilated) Length of intensive care unit (ICU) stay in a subset of children admitted to ICU Length of hospitalisation
Around 4–6 weeks after discharge from acute care	Strength and Difficulties Questionnaire (SDQ) Adaptive Behavior Assessment System-Second Edition (ABAS-II) Peds Quality of Life scoring algorithm Liverpool Outcome Score Gross Motor Function Classification System (GMFCS)
Around 6 months (±4 weeks) after randomisation	GOSE-Peds
Around 12 months (±4 weeks) after randomisation	New diagnosis of epilepsy Use of antiepileptic treatment Strength and Difficulties Questionnaire (SDQ) Adaptive Behavior Assessment System-Second Edition (ABAS-II) Peds Quality of Life (PedsQoL) scoring algorithm Liverpool Outcome Score (LOS) Gross Motor Function Classification System (GMFCS) Blinded neuropsychologist assessment of cognitive functioning using age appropriate developmental scales (Bayley Scales for Infant Development (BSID-III)/Wechsler preschool and Primary Scale of Intelligence III (WPPSI-III)/Wechsler Intelligence Scale for Children IV (WISC-IV)
12 months after randomisation	Proportion of deaths occurring in participants
Radiological	
Around 6 months after randomisation	Brain MRI to assess lesion resolution, presence of new lesions and distribution of persisting disease
Safety	
24–48 hours after the second IMP dose	Full blood count check to monitor for haemolysis
First 5 days after each dose of trial treatment	Adverse events of special interest (AESIs)
Up to 6 months after randomisation	Serious adverse events (SAEs)
Up to 12 months after randomisation	Serious adverse reactions (SARs)Suspected Unexpected Serious Adverse Reactions (SUSARs)
Autoimmune	Presence of and comparison of levels of specific neuronal antibodies in serum and/or CSF samples (where lumbar puncture is performed as part of routine care) before and after administration of trial treatment
*Tertiary outcomes*	Correlate MRI findings with neurological outcomes Correlate clinical and laboratory parameters with neurological outcomes Comparison of brain MRI findings with aetiological diagnosis Identification of specific DNA sequence and structural genetic variants in patients with encephalitis The following will be assessed before and after receipt of trial treatment: Comparison of inflammatory cytokines Assessment of regulatory T-cell frequency and function in blood and/or CSF Measurement of inflammatory markers in blood and/or CSF Analysis of gene expression in whole blood Comparison of the host inflammatory pathways and correlation with clinical parameters

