#### Neuropsychology assessment

This will be performed at 12 months after randomisation by a blinded trial neuropsychologist using age appropriate, validated scales of developmental assessment (see table 1).

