### Statistical methods

The primary statistical analysis will be carried out on the basis of ITT. After randomisation, participants will be analysed according to their allocated treatment group irrespective of what treatment they actually receive. However, a further modified ITT analysis will be performed excluding participants found to be ineligible in retrospect.

Data analysis will be performed using a mixed effect model for repeated measures, that is, to incorporate all outcome data collected during the 12 months follow-up, in order to apply the ITT principle as far as possible and to account for potential biases arising from loss to follow-up. The model will include treatment group, time, treatment-by-time interaction and baseline covariates. An unstructured correlation matrix will be used to model the within-participant error correlation structure. An appropriate contrast will be specified to test for treatment efficacy between randomised groups at 12 months. Various sensitivity analyses will be performed using other imputation methods, as well as analysis of 12-month data cross-sectionally, to test whether the results are robust to different assumptions about the missing data. The primary ITT analysis will account for steroid use before randomisation as a covariate. As required, the impact of posthospitalisation course including the use of concomitant and/or different immune treatments and period of neurorehabilitation on the primary outcome will be investigated in an exploratory analysis.

The results from the trial will be prepared as comparative summary statistics (difference in response rate or means) with 95% CIs. All the tests will be performed at a 5% two-sided significance level. A full detailed analysis plan (including plans for any interim analysis, subgroup analysis and sensitivity analysis) will be prepared and finalised before the first interim analysis.

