#### Secondary and tertiary analyses

As far as possible, we will use similar method for secondary and tertiary continuous outcomes collected at multiple time points or analysis of covariance for those collected at 12 months only, adjusting for baseline measures (if collected) and any stratification variables. Otherwise, an equivalent non-parametric method will be used for outcomes that violate the normal distribution assumption. A log-binomial regression will be performed on binary outcomes with similar adjustment of baseline covariates. χ^2^ or Fisher's exact test will be used to analyse AEs and non-adherence.

Reporting of the trial findings will be in line with Consolidated Standards of Reporting Trials (CONSORT) guidelines.

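### The 12-month cognitive score has no stated place for children who are too impaired to be tested or who have died; if they are left out, the comparison is biased against a treatment that helps the worst-affected

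*Protocol article*

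**What the plan says.** In Table 1 of the protocol article the cognitive outcome at 12 months is "Blinded neuropsychologist assessment of cognitive functioning using age appropriate developmental scales", using BSID-III, WPPSI-III or WISC-IV. The Neuropsychology assessment section fixes the timing: "This will be performed at 12 months after randomisation by a blinded trial neuropsychologist". Table 2 marks the assessment at that visit only, so there is no baseline or interim cognitive score.

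For continuous outcomes of this kind, Secondary and tertiary analyses names "analysis of covariance for those collected at 12 months only, adjusting for baseline measures (if collected) and any stratification variables". The alternative depends on distribution alone: "an equivalent non-parametric method will be used for outcomes that violate the normal distribution assumption". On missing data, Statistical methods says in general terms that "Various sensitivity analyses will be performed using other imputation methods".

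Death is a separate secondary outcome ("Proportion of deaths occurring in participants") and is not linked to the cognitive comparison. The abstract describes childhood encephalitis "with a 7% death rate and up to 50% morbidity after prolonged follow-up". The article gives no score, category or rank for a child who is alive but too impaired to complete the scale, or for one who has died.

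**The concern.** For a performance test, the absence of a score can be the worst result. Whether a child can be tested at 12 months is decided after randomisation and depends on cognition, which is what treatment is meant to change. Suppose IVIG moves some children from untestable to low-scoring. They enter the IVIG mean with low scores, while comparable placebo children contribute nothing. Both groups are then randomised groups cut down by an effect of treatment.

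The trial's main protection against incomplete follow-up is the repeated-measures model. It cannot use an earlier cognitive score here, because none exists. Imputation helps only if it does not assume that untested children resemble tested ones. At stake is a secondary result that could look null, or point the wrong way, beside a favourable primary result that the secondary outcomes are meant to support.

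**Working it through.** **The plan's own figure.** No sample size or effect is stated for cognition, so the only figure to reproduce is the primary sample size. It sets the number available. Reading the 20% difference as absolute (43% against 63%), with two-sided 5% significance and 90% power:
- n = [1.96√(2×0.53×0.47) + 1.2816√(0.43×0.57 + 0.63×0.37)]² / 0.20² = 128.8 per arm.
- The continuity correction gives 128.8/4 × [1 + √(1 + 4/(128.8×0.20))]² = 138.6, so 139.
- 139/0.90 rounds up to 155 per arm, 310 in total, against 308 stated. This reproduces and is not affected by the point.

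**Size of the bias: inputs.** All are assumptions: placebo scores normal with mean 90 and SD 20, a true IVIG gain of 5 points, and children below a fixed level c untestable. The mean among tested children is μ + 20λ, where λ = φ(a)/(1 − Φ(a)) and a = (c − μ)/20.

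| Placebo untestable | c | Placebo mean, tested | IVIG mean, tested | Observed difference | Loss of the 5 points |
|---|---|---|---|---|---|
| 0.6% | 40 | 90.35 | 95.18 | 4.83 | 3% |
| 5% | 57.1 | 92.17 | 96.36 | 4.19 | 16% |
| 10% | 64.4 | 93.90 | 97.63 | 3.73 | 25% |
| 15% | 69.3 | 95.49 | 98.87 | 3.39 | 32% |
| 20% | 73.2 | 97.00 | 100.10 | 3.10 | 38% |

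The last two rows need every child scoring below about 69 or 73 to be untestable, which is hard to credit. The first three rows are the safer range.

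**A second model, with rescue of the worst children.** The 7% deaths come from the abstract. The rest is assumed: testable mean 90, rescued children averaging 55, untestable survivors set to a floor of 40. Let untestable fall from 10% on placebo to 5% on IVIG.
- Rescue only, scored children: (0.05×55 + 0.83×90)/0.88 − 90 = −2.0. Survivors with the floor score: (0.05×40 + 0.05×55 + 0.83×90 − 0.10×40 − 0.83×90)/0.93 = +0.8.
- Rescue plus 5 points in testable children, scored children: (0.05×55 + 0.83×95)/0.88 − 90 = +2.7. Survivors with the floor score: (0.05×40 + 0.05×55 + 0.83×95 − 0.10×40 − 0.83×90)/0.93 = +5.3.

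The direction is the same as in the first model, and the sign can reverse when benefit lies only in the worst children.

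**What ranking does to power (first model).** Of 139 per arm, 7% deaths leave about 129 survivors.
- Scored children only, with variance 400(1 + aλ − λ²) in each arm: at 5% untestable SE = 2.33, z = 4.19/2.33 = 1.80, power about 44%. At 10%, SE = 2.24, z = 3.73/2.24 = 1.66, power about 38%.
- Ranking all survivors, ignoring ties: P(IVIG > placebo) = Φ(5/(20√2)) = 0.570, SE = √(259/(12×129²)) = 0.036, z = 1.95, power about 50%.
- Adding deaths at the bottom, 7% in both arms: P = 0.93²×0.570 + 0.93×0.07 + 0.5×0.07² = 0.561, SE = √(279/(12×139²)) = 0.0347, z = 1.75, power about 42%.

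Ranking therefore removes the bias. It gains power over scored-only at 10% untestable but not at 5% once equal deaths are included. In the second model with rescue only, a rank analysis including deaths had 3% to 5% power across untestable rates from 5% to 20%.

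**The case against.** The strongest reply is that this is a rule not shown rather than a wrong rule. The article condenses a longer protocol, defers to a detailed analysis plan, and promises sensitivity analyses under different missing-data assumptions. A floor score or lowest rank may already be written there. That limits the point, and several stronger readings fall with it.

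- A reader might infer that untestable children are excluded. The article never says so.
- A reader might infer that the reason for a missing score goes unrecorded. The neuropsychology form and case report form are not shown.
- A reader might infer that imputation would treat untested children like tested ones. No method is specified, and GOSE-Peds, ABAS-II, GMFCS and the Liverpool Outcome Score could inform a better one.
- A reader might infer that a benefit in the worst children would be hidden from the whole trial. Those four measures and deaths are all collected at 12 months and do not require the child to complete a cognitive battery. The binary primary outcome, cut at a GOSE-Peds score of 2, would not itself register movement among the worst children, but the scale and the other measures remain available.
- A reader might take "up to 50% of survivors reporting deficits such as memory loss, seizures, learning disability and functional impairment" as a guide to the untestable rate. It mixes many kinds of deficit and says nothing about testability.

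What stands is that the article does name an analysis for this outcome. That analysis needs a number from each child, and its rank alternative is triggered by non-normality, not by children without a score.

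**Conclusion.** The point holds conditionally. The stated method gives no place to children untestable through impairment or dead. If they have no score, the cognitive comparison is conditioned on a consequence of treatment and is biased against a treatment that helps the worst-affected. On the assumed mean of 90, SD of 20 and gain of 5 points, the loss is about 3% at 0.6% untestable, 16% at 5% and 25% at 10%. The true rate is unknown, so these figures show a range and are not an estimate. The primary analysis and the sample size of 308 are unaffected. If the full protocol or analysis plan already contains a rule, confirming it settles the matter.

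**What to change.** 1. Have the neuropsychologist record why a cognitive score is absent: too impaired, as against refusal or non-attendance.
2. Report the number untestable through impairment in each arm.
3. Prespecify a rank-based comparison in which deaths rank lowest and children untestable through impairment rank next, below all tested children. Show it beside the analysis of covariance in tested children, labelled as applying to tested children only.
4. Amend Secondary and tertiary analyses so that the rank method for this outcome is not triggered only by non-normality.

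The cost is one reason code and some analysis wording, with no new visits or staff, since the neuropsychologist already attends the 12-month visit. The downside is that a rank result is harder to interpret than a difference in points. Deaths that are equal between arms dilute it, and it does not guarantee power if benefit is confined to the worst children.
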